### Study description and study design

This multicenter study is an investigator-initiated, prospective randomized controlled trial (RCT) and follows a double-blinded (patient and investigator) study design with a parallel two-arm interventional model. As an intervention, we apply tDCS with CE-certified DC-Stimulators (NeuroConn, Ilmenau, Germany). In the context of motor rehabilitation after stroke, the clinical trial adheres to the German medical device law (Medizin-Produkte Gesetz, MPG; §23b).

We assume that the verum stimulation (anodal tDCS over the left parietal lobe) leads to a more significant improvement in apraxia severity than sham stimulation [1]. The primary endpoint is the difference in the total score of the Cologne Apraxia Screening (KAS [19]) between the post-interventional investigation and baseline. Thus, the null and alternative hypotheses are:
**H**_**0**_**:** The change of the motor-cognitive apraxic deficits (as assessed by the KAS) between the baseline assessment and the post-interventional assessment is the same in both treatment groups (verum tDCS and sham tDCS).**H**_**1**_**:** The change of the motor-cognitive apraxic deficits (as assessed by the KAS) between the baseline assessment and the post-interventional assessment is different in the verum tDCS group than in the sham tDCS group.

A pilot study following the identical interventional and training procedure was performed before this RCT [1]. Here, 20 apraxic patients showed a standard deviation (SD) of about 7 points in the comparison of the KAS-score between baseline and post-interventional assessment. The difference between the sham- and the verum-interventional group was 4.6 points. Based upon these data, a sample size of 50 per study arm is required to ensure a difference in effect of 4 points at an SD of 7 in a two-sample t-test at a level of significance of 0.05 and a power of 0.8. We added 10% for eventual non-parametric testing, leading to 55 patients per study arm or a total of 110 patients in the intention-to-treat (ITT) collective. Additional participants replace drop-outs that do not fulfill the ITT-criteria (i.e., drop-out before first stimulation).

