The primary collective for the analyses is the ITT collective, including all patients with the baseline KAS-score and the application of at least one stimulation. The secondary per-protocol (PP) collective includes all patients with a baseline and post-interventional KAS-score, plus the application of the verum or sham intervention according to the protocol, with the possibility of missing one stimulation, i.e., at least 4/5 stimulations must have been completed. The descriptive analysis will be conducted for the entire study cohort and both study groups. Two-sided statistical tests will be performed with the level of significance set to 0.05. The analysis of effectiveness will primarily be carried out in the ITT population “as randomized”. The PP population (at least 4/5 stimulations received) will be assessed for the sensitivity analysis. The analysis of safety will be conducted in the population “as treated” (at least 1/5 stimulations received).

Including screening, nine study visits are scheduled, eight of which are handled during the inpatient treatment in the neurological rehabilitation centers. The final, ninth (follow-up) visit can also take place at the patient’s home.

The primary outcome measures are collected at three time points: (1) baseline, i.e., in the week before stimulation, (2) post-intervention, i.e., in the week after stimulation, (3) follow-up, i.e., about three to four months after the stimulation. If patients assent, the neuropsychological and motor tests are recorded on video and re-evaluated for interrater-reliability. Please see the study flow chart Fig. 1 and Table 1 for the time points of the scheduled study visits and the respective motor and neuropsychological tests.

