### Arms and interventions

After inclusion in the study, participants are randomized in the proportion 1:1 to both study arms, following a stratification by KAS-Score (i.e., apraxia severity; < 68 / ≥ 68 points), age (< 65 / ≥65 years), and site of investigation (Rehabilitationszentrum Godeshoehe e.V., Bonn / MediClin Fachklinik Rhein/Ruhr, Essen).

In the experimental group, anodal tDCS at an intensity of 2 mA is applied for 10 min on five consecutive days. The anodal rubber electrode (size: 5x7cm, 35cm^2^) is placed over the left PPC at position P3 of the 10/20 EEG system, the reference electrode (size: 5x10cm, 50cm^2^) is located supraorbitally on the right forehead. Electrodes are inserted into sponges and dampened with a saline solution to optimize electrode-skin-interface. To fix the electrodes, a rubber band is placed around the head in addition to the EEG cap.

To avoid sudden current changes, a fade-in and fade-out phase is applied, in which the current increases/decreases. Following the recommendation of the NeuroConn company, we ensured that the change of current is less than 0.5 mA per second. Therefore, we used fade-in and fade-out periods of 6 s duration each, resulting in a change of current of 0.5 mA/1.5 s (= 0.333 mA/s, see Fig. 2). During the stimulation, the patient is instructed to sit relaxed in a chair with eyes either closed or opened, without falling asleep (offline-stimulation).

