To evaluate safety and tolerability of the stimulation, all participants receive a questionnaire after the five tDCS sessions about the occurrence of side / adverse effects of stimulation, their severity (1 = absent to 4 = severe), and the association of a putative adverse reaction with the test product (1 = none to 5 = definite). The questionnaire is based on a recommendation by Brunoni and colleagues to systematically assess the safety of tDCS [6]. For all (serious) adverse events ([S]AE), group comparisons are performed with Chi-square (or Fisher-exact) tests for the absolute occurrence as well as severity or causality. Further, to evaluate blinding efficacy, we ask the patients to ‘guess’ whether they received the ‘verum’ or the ‘sham’ stimulation (after all five stimulations have been performed). Further, patients are asked to provide a confidence rating for their guess regarding verum/sham tDCS.

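### Adverse events are compared between arms by significance tests with no effect estimate named; a risk difference with a 95% interval would show how much excess harm about 55 patients per arm can exclude.

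*Protocol article*

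**What the plan says.** In the protocol article, the section on outcome measures describes how safety and tolerability are evaluated. All participants complete a questionnaire after the five sessions, with severity graded 1 to 4 and relation to the stimulation graded 1 to 5. For adverse and serious adverse events, "group comparisons are performed with Chi-square (or Fisher-exact) tests for the absolute occurrence as well as severity or causality".

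The section on study description and design adds three elements:
- The safety set: "The analysis of safety will be conducted in the population “as treated” (at least 1/5 stimulations received").
- The test level: "Two-sided statistical tests will be performed with the level of significance set to 0.05".
- A descriptive analysis of the whole cohort and of each arm.

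The sample size rests on the KAS change alone: "a sample size of 50 per study arm is required to ensure a difference in effect of 4 points at an SD of 7". That calculation assumes a t-test with alpha 0.05 and 80% power. Ten per cent is then added, "leading to 55 patients per study arm or a total of 110 patients in the intention-to-treat (ITT) collective". The section on arms and interventions states that "participants are randomized in the proportion 1:1 to both study arms".

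The article names no risk difference, interval or harm margin. It also gives no expected event rates.

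**The concern.** A safety evaluation should say how much excess harm the data can exclude. A two-sided test at 0.05 does not say this. It reports whether a difference was shown, and in a trial sized for another endpoint it will often report that none was shown when one exists. Description by arm gives the two percentages but does not bound the difference between them.

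The article presents tDCS as an add-on to regular rehabilitation. If the KAS result is positive, the benefit has to be weighed against an excess risk and its uncertainty. The named comparison supplies neither.

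**Working it through.** **Inputs from the article.** KAS difference 4, SD 7, alpha 0.05 two-sided, power 0.80, 1:1 allocation, 55 per arm. The safety set is taken as about 55 per arm, because the ITT set also requires at least one stimulation.

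**Assumed inputs.** Event rates, with one yes/no outcome per patient. Sham rates run from 0% to 40%.

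**Step 1: the article's own figure.** The normal approximation is n = 2 × (1.960 + 0.842)² × 7² / 4² = 48.1, so 49 per arm. The exact t-test solution is 49.05, so 50 per arm (power 0.808). Then 50 × 1.1 = 55. The stated size reproduces. No power is stated for safety.

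**Step 2: power of the named tests.** Let X and Y be the numbers of patients with an event under verum and sham: X ~ Bin(55, p_v), Y ~ Bin(55, p_s), independent. Power is the sum of P(X = x)·P(Y = y) over those of the 56 × 56 pairs with p ≤ 0.05. The miss rate is 1 − power. Chi-square is uncorrected.

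| Sham vs verum | Excess (points) | Miss rate, Fisher | Miss rate, chi-square |
|---|---|---|---|
| 0% vs 5% | 5 | 94% | 70% |
| 5% vs 10% | 5 | 92% | 84% |
| 0% vs 10% | 10 | 52% | 19% |
| 2% vs 12% | 10 | 63% | 44% |
| 5% vs 15% | 10 | 72% | 58% |
| 10% vs 20% | 10 | 78% | 69% |
| 20% vs 30% | 10 | 83% | 77% |
| 5% vs 25% | 20 | 20% | 13% |
| 10% vs 30% | 20 | 32% | 23% |
| 20% vs 40% | 20 | 44% | 36% |
| 30% vs 50% | 20 | 51% | 42% |
| 40% vs 60% | 20 | 53% | 46% |

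The excess detectable with 80% power (Fisher / chi-square) is about 14 / 10 points at a sham rate of 0%, 20 / 18 at 5%, 23.5 / 21 at 10%, 26.5 / 24.5 at 20% and 28.5 / 26.5 at 30%.

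The favourable chi-square figure for 0% versus 10% carries a caveat. The expected number of events per arm is then 55 × 0.05 = 2.75, a sparse setting in which Fisher is the customary choice. The article does not say when each test applies.

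**Step 3: what an interval would show.** The Newcombe interval for d = p̂_v − p̂_s uses the Wilson limits (l, u) of each arm. The lower limit is d − √[(p̂_v − l_v)² + (u_s − p̂_s)²]. The upper limit is d + √[(u_v − p̂_v)² + (p̂_s − l_s)²].

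For 5/55 versus 0/55, p̂_v = 0.0909 with Wilson limits 0.0395 and 0.1958, and p̂_s = 0 with limits 0 and 0.0653:
- Lower limit: 0.0909 − √(0.0514² + 0.0653²) = 0.008.
- Upper limit: 0.0909 + √(0.1049² + 0²) = 0.196.

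| Events, verum vs sham | Fisher p | Risk difference (points) | 95% interval (points) |
|---|---|---|---|
| 0 vs 0 | 1.00 | 0 | −6.5 to +6.5 |
| 1 vs 1 | 1.00 | 0 | −7.9 to +7.9 |
| 5 vs 0 | 0.057 | +9.1 | +0.8 to +19.6 |
| 8 vs 3 | 0.20 | +9.1 | −2.6 to +21.2 |
| 10 vs 5 | 0.27 | +9.1 | −4.1 to +22.3 |
| 20 vs 11 | 0.09 | +16.4 | −0.5 to +32.0 |

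Every row is non-significant by Fisher, but the upper limits run from 6.5 to 32 points. The p-value alone does not convey that range.

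**The case against.** **Level of detail.** The document is a condensed article. Intervals for adverse-event tables are commonly left to a full protocol or SAP, and neither is shown. The article names no interval for the KAS comparison either. This stands: the absence of an interval is not an error, and chi-square and Fisher are valid tests of two proportions. It does not remove the suggestion, because the article does state its between-arm safety method, and a better summary is available from the same data.

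**Stronger readings that the article does not support.**
- A reader might infer that safety is compared only on the occurrence of events. The quoted sentence also covers severity and causality, and description by arm is planned.
- A reader might infer that the tests would miss most relevant harm. The article gives neither event rates nor a relevant excess. With sham rates of 5% to 30%, an excess of about 20 to 28 points (Fisher) is detected with 80% power.
- A reader might infer that a non-significant test will be reported as proof of safety. No sentence says so. The hypotheses concern the KAS only, and the perspective section draws no safety conclusion.

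**Limits of the remedy.** An interval adds no information beyond the same 55 per arm, and no margin is defined against which to judge the upper limit. Both are true. The gain is that the uncertainty is shown. Fisher and the Newcombe interval can also disagree, as with 5 versus 0, which is why one of them should be named as the main summary.

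**Conclusion.** The point holds as a low-cost improvement to a stated method. With about 55 per arm, an excess of 5 to 10 points would usually be missed. The exception is a 10-point excess over a sham rate of about 0% to 2% tested by chi-square (power 81% at 0%, 56% at 2%). Excesses of 20 points are detected more often than not at sham rates up to 20%. At 30% and 40% Fisher falls just short of even odds (power 0.49 and 0.47), while chi-square stays above.

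A non-significant test would therefore not support a statement of no excess harm. All these figures rest on assumed event rates, one binary outcome per patient and full arms of 55.

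**What to change.** In the safety paragraph of the outcome measures section, or in the SAP if it is not already there, specify the following:

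- For patients with at least one adverse event, at least one serious adverse event, and each questionnaire item, report the proportion per arm and the risk difference (verum minus sham). Give a two-sided 95% Newcombe or exact interval. Count each patient once, in the as-treated set.
- Make this the main between-arm safety summary, with the chi-square or Fisher p-value as a supplement.
- Word the safety conclusion by the upper limit, meaning the largest excess risk compatible with the data. State that non-significance will not be taken as evidence of safety.

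The cost is one or two sentences, with no new data, visits or patients. The downside is a less favourable safety statement, because the intervals are wide: about ±6.5 to ±8 points even with 0 or 1 event per arm.

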### Eligibility criteria

The criteria for inclusion in the study are defined as follows: (i) age between 18 and 90 years, (ii) LH ischemic stroke in the subacute/ chronic phase (here: > 10 days and < 180 days post-stroke), (iii) clinical presentation of apraxia in the Cologne Apraxia Screening (KAS; cut-off ≤76/ 80 points), and (iv) written informed consent by the patient or the legal guardian.

The criteria for exclusion of the study are defined as follows: (a) inability of the stroke patient to provide informed consent; in case of a legal guardian: the legal guardian is not available or declines consent; (b) pregnancy and breastfeeding; (c) patients with clinically manifest stroke before the index stroke; (d) malignant disease with affection of the central nervous system; (e) estimated life expectancy < 12 months; (f) current alcohol or drug addiction or other addictive disease (exception: nicotine); (g) current clinically manifest psychiatric disorders, such as schizophrenia or severe depressive episode; (h) epileptic seizure within the past two years; (i) intake of anti-epileptic drugs for prophylaxis of epileptic seizures; (j) continuous medication during the interventional phase with benzodiazepine or antipsychotics of high potential; (k) enrollment in other studies with brain stimulation in the period after the index stroke; (l) heart pacemaker; (m) electrodes for deep brain stimulation or other metal implants in the head; (n) craniectomy or cranial trepanation; (o) vulnerable skin lesions at planned electrode positions; and (p) poor motivation or cooperation.

In this study, LH stroke patients with apraxia are recruited during their inpatient stay in rehabilitation centers. The index stroke is diagnosed according to clinical standards (preferably including neuro-imaging with either cerebral computed tomography (CT) or cerebral magnetic resonance imaging (MRI)). If the patient provides written consent, the corresponding brain scans are obtained from the primary hospital and will be used for lesion mapping in the final reporting.

Patients with LH stroke are screened by the investigator (medical doctor). For the screening procedure, written informed consent is obtained. After that, inclusion and exclusion criteria are checked, and the KAS, the ACL-K, the EHI, and the HADS are applied. In case that all eligibility criteria are met, the patient is informed about the study procedures in detail, the interventional product, including potential side effects, and the randomization procedure. The study informed consent form, including the insurance documents, is handed to the patient. Then, time for consideration of at least 24 h is given until study inclusion takes place. In the case of a legal guardian, the procedure is carried out with the guardian and patient together.

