**Methods:**

Based on promising results of a pilot study, the on-going RAdiCS (**R**ehabilitating stroke-induced **A**praxia with **di**rect **C**urrent **S**timulation) study is a randomized controlled trial, which follows a double-blinded (investigator and patient), two-arm parallel interventional model. It is designed to include 110 apraxic patients (as diagnosed by the Cologne Apraxia Screening, KAS) in the subacute phase after a left hemisphere (LH) stroke. The University of Cologne initiated the trial, which is conducted in two German Neurorehabilitation Centers.

The study aims to evaluate the effect of anodal (versus sham) transcranial direct current stimulation (tDCS) applied over the left posterior parietal cortex (PPC) with an intensity of 2 mA for 10 min on five consecutive days on apraxic deficits. In addition to anodal or sham tDCS, all LH stroke patients undergo a motor (cognitive) training that is performed before and after the stimulation (off-line stimulation).

The primary outcome measure is the (differential) change in the overall KAS score after five daily sessions of anodal versus sham tDCS when compared to the baseline assessment before tDCS. Secondary study outcomes include further apraxia scores, aphasia severity, and measures of motor performance and disability after stroke. All outcome measures are obtained in the post-stimulation assessment as well as during follow-up (3–4 months after tDCS).

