## Methods

### Aim of the trial

A randomized controlled trial (RCT) on the utility of tDCS in apraxia is still missing. Thus, the RCT RAdiCS (Rehabilitating stroke-induced Apraxia with direct Current Stimulation) aims to investigate whether (in addition to motor (cognitive) training) repetitive anodal tDCS applied above the left, ipsilesional PPC can facilitate the recovery of the motor cognitive deficit apraxia during neurorehabilitation in the subacute to chronic phase after LH stroke.

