### Outcome measures

The primary outcome measure is the change of the total score of the Cologne Apraxia Screening (KAS [19];) achieved post-interventionally, compared to the patient’s baseline performance. The KAS is a reliable and valid screening tool [8], assessing bucco-facial and limb apraxia with two types of tasks (pantomime of tool use and imitation). The primary analysis is the comparison of the difference in the KAS-score changes between the two study arms (verum vs. sham stimulation) with a t-test in the ITT collective. If necessary, equivalent non-parametric methods are applied. The differences in KAS-score changes between follow-up and post-interventional assessments, as well as between follow-up and baseline assessments, are compared to evaluate a long-term effect. An analysis of variance (ANOVA) with the factor treatment and the co-factors age, KAS-score classification at baseline, and study site will investigate potential influences of the randomization strata on the treatment effect.

Secondary outcome measures are the changes in the additional neuropsychological and motor tests. Further apraxia assessments include the De Renzi test of actual object-use, the De Renzi imitation test, as well as the Goldenberg hand- and finger-imitation test. Moreover, aphasia is assessed by the short version of the Aphasia Check List (ACL-K). For general motor performance, the force of hand extension is assessed bimanually with the Medical Research Council (MRC) paresis scale, and the grip force is measured with a Vigorimeter (Martin Vigorimeter, medium-sized ball). Furthermore, the Action Research Arm Test (ARAT) is applied to both hands, and the Jebsen Taylor Hand Function Test (JTHFT) is applied to the ipsilesional (left) hand. To document the overall disability after stroke, we use the modified Ranking Scale (mRS).

As (cognitive) motor training, the ARAT, the De Renzi Imitation Test, and JTHFT are conducted before and after the stimulation sessions on the five interventional study visits (S1-S5 = T2-T6).

Additionally, the National Institutes of Health Stroke Scale (NIHSS), the Edinburgh Handedness Inventory (EHI), the Hospital Anxiety and Depression Scale (HADS), and the educational background are assessed at study inclusion.

Secondary outcome measures are assessed at the same time points as the primary outcome measures, i.e., at baseline, post-intervention, and follow-up, and are analyzed analogously to the primary outcome measures (see above).

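### Time since stroke (day 11 to day 179 at entry) is in none of the analyses described, so some precision in the KAS comparison may be given away at no saving

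*Protocol article*

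**What the plan says.** - **Entry window.** Eligibility criteria: left-hemisphere ischaemic stroke, "here: > 10 days and < 180 days post-stroke", which is day 11 to day 179.
- **Randomisation.** Arms and interventions: 1:1, "following a stratification by KAS-Score (i.e., apraxia severity; < 68 / ≥ 68 points), age (< 65 / ≥65 years), and site of investigation". Time since stroke is not a stratum.
- **Primary analysis.** Outcome measures: "comparison of the difference in the KAS-score changes between the two study arms (verum vs. sham stimulation) with a t-test in the ITT collective", with a non-parametric equivalent if needed. Changes involving the follow-up visit are compared as well.
- **Covariate model.** Outcome measures: "An analysis of variance (ANOVA) with the factor treatment and the co-factors age, KAS-score classification at baseline, and study site", used to examine whether the strata influence the treatment effect. Secondary outcomes follow the same scheme.
- **Population wording.** The aim is set "during neurorehabilitation in the subacute to chronic phase after LH stroke"; the abstract describes patients "in the subacute phase after a left hemisphere (LH) stroke".

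**The concern.** The primary endpoint is a change score in a deficit that may also improve without stimulation. The aim itself speaks of facilitating recovery, and the Perspective section rests clinical relevance on apraxia that persists beyond the acute phase. The latest permitted entry is about 16 times as far from the stroke as the earliest (179/11 = 16.3). If natural gain between baseline and post-intervention depends on where in that window a patient enters, the differences go into the error term of an unadjusted t-test. They also stay in the error term of an ANOVA limited to "co-factors age, KAS-score classification at baseline, and study site". A covariate known before treatment could remove part of that variation. At stake is the width of the confidence interval for the KAS difference, and with it power.

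**Working it through.** **Inputs from the article (Study description and study design; Arms and interventions):** difference 4 points, SD 7, two-sided 0.05, power 0.80, 1:1 allocation, 50 per arm raised by 10% to 55.

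**Step 1: the plan's own figure.** The two-sample t-test with the noncentral t distribution gives power 0.7996 at 49 per arm and 0.8076 at 50, so 50 is right. 50 × 1.1 = 55. Power at 55 per arm is 0.844. The standard error of the KAS difference is 7 × √(2/55) = 1.33 points.

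**Step 2: assumptions not in the documents.** Natural gain over the study interval for a patient entering on day t is taken as G × exp(−(t − 11)/τ), where G is the gain at day 11 (2 to 10 points) and τ is 30, 45 or 60 days. Entry day is either uniform over 11 to 179, or skewed early (11 plus an exponential with mean 35 days, capped at 179). SD 7 is taken to contain this variation already.

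**Step 3: formulas.** R² = SD(gain)²/49. Adjusted SD = 7 × √(1 − R²). Adjusted SE = adjusted SD × √(2/55). Power is for 4 points at 55 per arm with one degree of freedom lost (107). Each range covers all τ and both entry patterns.

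| G (points) | SD of gain | R² | Adjusted SE | Power |
|---|---|---|---|---|
| none (unadjusted) | – | – | 1.33 | 0.844 |
| 2 | 0.48–0.59 | 0.005–0.007 | 1.33 | 0.845–0.846 |
| 4 | 0.96–1.18 | 0.019–0.028 | 1.32 | 0.850–0.854 |
| 6 | 1.44–1.77 | 0.042–0.064 | 1.29–1.31 | 0.859–0.866 |
| 8 | 1.92–2.36 | 0.075–0.114 | 1.26–1.28 | 0.870–0.884 |
| 10 | 2.40–2.95 | 0.118–0.178 | 1.21–1.25 | 0.885–0.906 |

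Top case written out: 2.95²/49 = 0.178; 7 × √0.822 = 6.35; 6.35 × √(2/55) = 1.21.

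**Step 4: does a log term capture the curve?** The table assumes that it is captured fully. Under these curves log(days) correlates with the gain at |r| of 0.96 to 0.997. In the top case |r| = 0.987, so R² becomes 0.178 × 0.987² = 0.173 and power 0.904. The range with the log term is therefore 0.845 to about 0.90.

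**Step 5: how plausible is the upper end?** The KAS has 80 points and entry requires 76 or less. A patient entering at 76 can gain at most 80 − 76 = 4 points, and one at the lower edge of the upper stratum at most 80 − 68 = 12. A mean natural gain of 6 to 10 points is out of reach or near the ceiling for many in that stratum, and the interval runs only from the week before stimulation to the week after. The lower rows cannot be dismissed.

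No figure can be given for T8, because the article states no SD for the change to follow-up.

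**The case against.** The strongest reply is that nothing here is wrong. Randomisation makes the t-test valid whatever the spread of entry times, and the hypotheses concern the average difference in the patients enrolled. Three binary strata already give 2 × 2 × 2 = 8 cells for 110 patients, and analysing by them is conventional. A further covariate could stand in a statistical analysis plan that is not shown. Most of this stands. What remains is that the article does not leave the matter open: it names the primary test, the one covariate model and each covariate, and a variable already in hand is not among them.

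A reader might infer more than the documents support:

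- **That chance imbalance adds a further error.** Under the model above the imbalance has an SD of SD(gain) × √(2/55), at most 2.95 × √(2/55) = 0.56 points. That variation is part of SD 7, hence already inside the standard error of 1.33 and allowed for by the test.
- **That the trial is underpowered.** This needs the pilot SD of 7 to exclude recovery variation, which the article does not say. Were it so, unadjusted power at 55 per arm would be 0.840, 0.829, 0.809, 0.777 and 0.730 for assumed correlations of 0.1, 0.2, 0.3, 0.4 and 0.5 between time since stroke and KAS change. It would fall below 0.80 only at the two highest values.
- **That the trial cannot support its subacute-to-chronic aim.** The eligibility criteria define the enrolled window in days, and a trial of an average effect need not show that the effect is constant across it. The abstract's shorter wording is an editorial matter.

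**Conclusion.** The point holds as a matter of efficiency. Time since stroke spans day 11 to day 179, is known for every patient, and is used in none of the analyses described. The planned test is valid, and the stated sample size and power reproduce. The possible gain from adjustment runs from nothing of note (0.845 against 0.844) to about six percentage points of power (about 0.90), with the standard error falling from 1.33 to 1.21 points at best. That range rests on the assumed recovery curve and on SD 7 already containing recovery variation. The documents give no recovery rate to narrow it, and the KAS ceiling argues against relying on the upper end. Baseline KAS class and age may also capture part of the same variation, which would shrink the gain further.

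**What to change.** Before unblinding, pre-specify log(days from stroke to first stimulation) as a continuous covariate, alongside KAS class, age and site, in the model comparing KAS change between arms at T7 and T8. State whether that model or the t-test is primary, since the precision gain reaches the primary result only if the adjusted model is. If the verum–sham difference is shown across time since stroke, label the display descriptive; an interaction test in 110 patients would have little power.

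The cost is analysis-plan wording and one degree of freedom. Eligibility already requires the time since stroke, and every patient in the ITT collective has had a first stimulation, so no new data are needed. Stratification, randomisation and sample size stay unchanged. Adding the covariate only after seeing an imbalance would be post hoc and carry less weight.

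### The unadjusted t-test on raw KAS change ignores baseline KAS, although the 80-point ceiling leaves patients entering at 68-76 only 4-12 points to gain

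*Protocol article*

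**What the plan says.** - **Scale and entry rule** (Eligibility criteria): "clinical presentation of apraxia in the Cologne Apraxia Screening (KAS; cut-off ≤76/ 80 points".
- **Randomisation** (Arms and interventions): 1:1, with "stratification by KAS-Score (i.e., apraxia severity; < 68 / ≥ 68 points", and also by age group and site. The same section says that both arms receive the motor training before and after stimulation on five days.
- **Primary analysis** (Outcome measures): "The primary analysis is the comparison of the difference in the KAS-score changes between the two study arms", by t-test in the ITT set, with a non-parametric equivalent if needed. A further ANOVA with treatment, age, baseline KAS class and site is meant to show whether the strata influence the treatment effect. Follow-up changes in KAS are also compared.
- **Sample size** (Study description and study design): "a sample size of 50 per study arm is required to ensure a difference in effect of 4 points at an SD of 7". The planned power is 80% and the tests are two-sided at 5%. A tenth more is added in case a rank test is needed, which makes 55 per arm and 110 in all. The inputs come from a 20-patient pilot with the same intervention and training, which saw a difference of 4.6 points and an SD of about 7.

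The article does not mention a ceiling. It gives neither the expected baseline KAS distribution nor the pilot's baseline range.

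**The concern.** A patient who starts near the top of the scale cannot show a large gain. Sham patients are trained and in rehabilitation, so they may improve too and use up some of the same room. If verum helps more, verum patients reach 80 more often, and the cap takes more from that arm. The observed mean difference then lies below the difference that an unbounded measure would show, by an amount that depends on how many mild patients enrol.

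Two readings of the result are at stake. The overall estimate may look weak for a treatment that works. The ANOVA by baseline KAS class may also show a smaller effect in mild patients that comes from the scale and not from the treatment. The non-parametric fallback does not help, since it ranks the same capped changes.

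Separately, a test on raw change leaves baseline KAS out of the model. If patients with larger deficits gain more, that variation stays in the error term.

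**Working it through.** **1. The plan's own figure.** Difference 4, SD 7, two-sided alpha 0.05, power 0.80. The noncentral-t calculation gives 49.05, rounded up to 50 per arm (power 0.808). 50 × 1.10 = 55 per arm, 110 in total. The stated figures reproduce. Power at 55 per arm is 0.844 for 4 points and 0.927 for the pilot's 4.6 points.

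**2. Headroom.** For baseline *b* and mean sham gain *g* at that baseline, the largest possible mean difference is 80 − *b* − *g*.

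| Baseline | Headroom 80 − *b* | Left if *g* = 2 | Left if *g* = 4 |
|---|---|---|---|
| 68 | 12 | 10 | 8 |
| 72 | 8 | 6 | 4 |
| 76 | 4 | 2 | 0 |

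At 76, a 4-point difference needs every verum patient to reach 80 and no mean gain under sham. With a sham gain of 4, it is out of reach above 72. The values of *g* are assumptions.

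**3. Constant latent effect.** Simulation with 55 per arm, 600 trials per scenario: post KAS = min(80, baseline + *g* + 4 × arm + N(0, SD 7)), rounded. Assumed, because not in the document: the share of patients at 68-76, *g*, and uniform baselines within 68-76 and 40-67. The censored (Tobit) model includes baseline KAS.

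| Share at 68-76 | *g* | Observed difference | t-test power | Censored-model power |
|---|---|---|---|---|
| 30% | 2 | 3.70 | 0.85 | 0.87 |
| 50% | 4 | 3.20 | 0.80 | 0.82 |
| 50% | 6 | 2.85 | 0.72 | 0.78 |
| 70% | 6 | 2.59 | 0.70 | 0.81 |

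The Monte Carlo standard error of a power near 0.8 is √(0.8 × 0.2 / 600) = 0.016, so 0.85 in the first row does not differ from the uncapped 0.84. Across these scenarios the difference is 2.0-2.9 at 68-76 and 3.8-4.1 below 68, and 11-38% of patients end at 80. The censored model estimates 4.0-4.1 points. Part of its gain in power over the t-test comes from including baseline, not from the censoring.

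A second grid (25, 50 or 75% mild; *g* = 0, 3 or 5; other baselines 30-67; 4,000 trials each) gives 2.6-3.8 points overall, 2.2-3.2 at 68-76, and power 0.72-0.82. The SD falls from 7 to as low as 5.4, which offsets part of the power loss.

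**4. Gains proportional to the deficit.** Here the gain is a multiple of 80 − *b*, scaled to an average sham gain of 4 and an average effect of 4, with 30-70% mild. With residual SD 3 (mild) and 8 (others), the observed difference is 3.7-4.0 and t-test power 0.80-0.83 (300 trials each). Over variants of this model the difference is about 3.5-4.0. Adjusting for continuous baseline KAS and the strata raises power from about 0.70-0.84 to about 0.86-0.98. In the constant-effect scenarios the same adjustment never materially lowered power.

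**5. What each model repairs.** Baseline is independent of arm by randomisation, so linear adjustment leaves the expected mean difference where it was and only improves precision. Only the censored model addresses the cap. With no treatment effect, the t-test rejected in 0.02-0.06 of simulated trials, and the censored model in about 0.05.

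**The case against.** The best counter-argument is that the endpoint is the observed change in KAS. For that quantity the t-test is valid: it estimates the mean difference in observed change and keeps its type I error. Attenuation exists only relative to a latent score above a perfect test result, which the trial does not define and which has no stated clinical meaning. This stands, and it is why the censored model belongs beside the primary analysis and not in its place.

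A reader might infer that the trial is underpowered. The document does not support that. The 4 points and SD of 7 come from observed pilot scores on the same 80-point scale, and 4 is below the pilot's 4.6. Applying the cap to these values again, as step 3 does, may count the ceiling twice. A milder case mix than in the pilot is possible, but nothing shows it.

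A reader might also infer that the analysis understates any tDCS effect. It does not: patients below 68 lose almost nothing, and step 4 shows that the overall loss nearly vanishes if gains scale with the deficit.

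Stratifying at 68 balances mild patients between arms, and the ANOVA looks at severity. Neither restores headroom. The ANOVA uses two KAS classes and is not the primary test.

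Finally, a censored model and counts at the ceiling are details that a statistical analysis plan may hold, and their absence from an article is not an error. The unadjusted t-test, however, is a choice that the article states.

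**Conclusion.** The concern holds in a limited form. The cap, the entry rule and the unadjusted t-test on raw change are all stated, and together they can attenuate an effect in patients entering at 68-76 and waste precision. If the latent effect is 4 points at every severity, about 2.6-3.7 would be observed overall; if gains scale with the deficit, about 3.5-4.0 of an average 4. Both ranges rest on an assumed baseline mix and sham gain, and the document cannot say which is nearer the truth. The case for baseline adjustment does not depend on that choice: it cost nothing material in one model and gained clearly in the other. No error in the sample size and no inflation of type I error is shown. The point is a worthwhile improvement to the analysis, not a defect that invalidates the trial.

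**What to change.** Before unblinding, keeping the KAS and the eligibility rule:

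1. Replace the unadjusted t-test as the primary comparison by a linear regression of post-interventional KAS (or KAS change) on treatment, continuous baseline KAS and the stratification factors (age group, site), in the ITT set.
2. Name a model right-censored at 80 with the same covariates as a sensitivity analysis at the post-interventional (T7) and follow-up (T8) assessments, and show it beside the raw mean difference.
3. Report the number of patients at 80 per arm at T7 and T8.
4. State that a smaller effect in the ≥68 stratum is not read as lower efficacy without the censored analysis.

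The cost is wording and two standard models. All covariates are already collected, and no patients or visits are added. The small downside is that the censored model assumes roughly normal latent scores and estimates an effect on the uncapped scale, so it should not stand alone.
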